In this study, the aim was to observe and analyze each participant’s adherence and device usage in their natural living environment without imposing any burden or obligation to use the device. Adherence, device usage, and the duration of recorded data will be reported as study outcomes to evaluate the practicality and real-world applicability of using a wearable device in individuals with COPD. Since one of the main challenges of wearable or medical devices in free-living conditions is maintaining consistent adherence, no fixed adherence target was predefined. Instead, the number of days and hours the device was worn will be reported as adherence outcomes. This approach enables assessment of device acceptability, user compliance, and usage patterns, particularly during eCOPD periods, during unsupervised, real-world conditions without external reminders or enforced wearing schedules.

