**Methods:**

This single-center feasibility study involves prospective physiological data collection with retrospective analytical evaluation of physiological changes occurring around clinically confirmed COPD exacerbations. A total of 30 participants with COPD (Modified Medical Research Council Grades 1‐4) who have experienced at least one exacerbation within the past 12 months will be included. Each participant will wear a continuous physiological monitoring device in their free-living environment for up to 18 months or until an eCOPD event occurs. The device will continuously collect physiological signals, including heart rate, respiratory rate, and heart rate variability. Data will be analyzed using statistical quality control methods, specifically the Cumulative Sum approach, to identify physiological deviations occurring within 7 days (168 h) prior to an exacerbation event. These findings will be correlated with clinical records and qualitative data. Qualitative information will be obtained through biweekly self-administered questionnaires assessing symptom changes and through additional adherence and usability questionnaires completed during home visits conducted every 2 weeks by the researcher.

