#### Study Assessments

A researcher will separately meet each participant every 2 weeks to monitor progress and enquire whether they have experienced any exacerbations that have required medical attention. Two questionnaires will be completed by the participant. A COPD symptom questionnaire is used to assess any changes in the participant’s symptoms as independent variables, including appetite, breathing, cough, energy levels, general wellness, and medication usage. In addition, a Device Usage and Adherence Questionnaire will evaluate the participant’s experience with the Frontier X2 device, focusing on ease of use, adherence to the study protocols, and any challenges they may have faced while using the device. Following the completion of the questionnaires, the researcher will address any technical issues related to the device or app, offer troubleshooting assistance, and answer any questions the participant may have about the study. These visits will ensure regular communication and allow the researcher to provide support, ensuring that participants are comfortable with the device and that any concerns are promptly resolved.

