### Study Device

The Frontier X2 is a chest-worn wearable device designed to monitor physiological parameters in real time. This compact device captures key metrics including HR, BR, HRV, continuous ECG, and physical activity, making it well-suited for continuous health monitoring. The device employs Bluetooth Low Energy technology for data synchronization and is IP67-rated, providing water resistance up to 1.5 m. It also meets international industry standards including International Electrotechnical Commission; International Organization for Standardization; Registration, Evaluation, Authorization and Restriction of Chemicals; Conformité Européenne; and Restriction of Hazardous Substances, ensuring regulatory compliance and durability.

Although initially developed for sports performance monitoring, the Frontier X2 incorporates features with strong relevance for clinical research, such as extended ECG recording and onboard vibration alerts. In this study, the device will be used in passive data collection mode, without real-time alerts being activated. Data are stored locally for up to 24 hours. Given the protocol requirements, participants will be asked to sync data daily via Bluetooth.

Previous studies have demonstrated that the Frontier device has the potential for disease management for people with different chronic diseases [28,29]. Ongoing and future research, including the present study, aims to contribute to the growing body of evidence regarding its accuracy, reliability, and potential applications in chronic disease management. Full specifications and an image of the Frontier X2 can be found at the manufacturer’s website [30].

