### Potential Challenges and Alternatives

The potential risks to participants are considered to be low or mild. Volunteers will have to continuously wear the device (Frontier X2). This may be associated with minor discomfort of the device being situated on their chest that may cause mild positional discomfort while undertaking certain activities, such as having to adopt an alternative sleeping position. The device is secured to the chest by an elastic chest strap, composed of a hypoallergenic material, although there is still a small possibility that it may cause a skin irritation if it is worn for prolonged periods in the same position.

The device has a battery life of 24 hours and can be fully recharged in 45 minutes. Users will be provided with the necessary equipment for charging the device and are expected to charge their device every 24 hours. This can be a burden for participants. Volunteers will be expected to complete a 10-minute symptom questionnaire every 2 weeks to see if this correlates with device biometric data capture. This questionnaire will be collected when the PhD researcher undertakes a site visit to the volunteer’s house to check the battery for the device and to provide any additional technical support. These would discontinue if there were any discomfort.

The non-invasive physiological measurements involve minimal burden.

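### Adherence is described as unsupervised and free of reminders, but wear time is only ever measured under fortnightly researcher visits, so it cannot support a conclusion about unsupported use

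*Protocol article*

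**What the plan says.** The last paragraph of Quantitative Analysis sets no adherence target and states that "the number of days and hours the device was worn will be reported as adherence outcomes". It says use is observed "without imposing any burden or obligation to use the device" and that the approach assesses acceptability, compliance and usage patterns "during unsupervised, real-world conditions without external reminders or enforced wearing schedules". The stated purpose is to judge how practical and how applicable the device is in real life. Adherence, usability and comfort form item 5 of the Secondary Objectives, and everyday usability is the first of the Secondary End Points.

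The contact schedule is set out in other sections:

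- Study Assessments: "A researcher will separately meet each participant every 2 weeks to monitor progress". Two questionnaires are completed, one of which asks about adherence to the study protocols. Afterwards "the researcher will address any technical issues related to the device or app, offer troubleshooting assistance".
- Abstract, Methods: the contact includes "additional adherence and usability questionnaires completed during home visits conducted every 2 weeks by the researcher".
- Potential Challenges and Alternatives: the researcher goes to the volunteer's house "to check the battery for the device and to provide any additional technical support". The same section says that volunteers have to wear the device continuously and are expected to recharge it once a day, and concedes that this may be burdensome.
- Monitoring: recorded data are reviewed at the scheduled fortnightly visits.
- Participant Training: guidance on use and upkeep continues for as long as the person takes part.

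**The concern.** The adherence result is meant to tell readers whether people with COPD would wear this device in ordinary life. A reader told that wear was unsupervised and unprompted would apply the reported hours to patients who are handed the device and left alone. The visit schedule describes a different setting: a researcher comes every fortnight, asks about adherence, fixes faults, checks the battery and looks at the data. Being asked about adherence every 2 weeks can reasonably be expected to act as a prompt, and fixing faults removes a common reason for stopping. If the label stays, a secondary outcome will be published as evidence about a condition that the study never observes.

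**Working it through.** The article gives no figure for this point, so there is none to reproduce. The check is a comparison of statements, followed by a count of contacts.

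**Statement by statement**

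| Property claimed in Quantitative Analysis | What other sections say | Result |
|---|---|---|
| Unsupervised | Fortnightly home visit with adherence questionnaire, troubleshooting, battery check and data review (Abstract, Study Assessments, Monitoring, Potential Challenges and Alternatives) | Not a property of the design |
| No external reminders | Alerts are switched off (Study Device, Monitoring) and no reminder message is described, but adherence is asked about in person every 2 weeks and guidance is ongoing (Participant Training) | True of automated reminders only; too broad as written |
| No enforced wearing schedule | Data Collection says wear-time expectations are not enforced | Consistent |
| No burden or obligation | Potential Challenges and Alternatives requires continuous wear, expects daily charging and calls this a possible burden | Contradicted |

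**Is there any unsupported wear to observe?** All 30 participants follow the same visit schedule, and it runs throughout follow-up. There is no unvisited group and no planned visit-free period. The contrast between wear with visits and wear without them therefore cannot be estimated from this study.

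**Amount of contact**

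1. Full follow-up: 18 months × 365.25/12 = 547.9 days; 547.9/14 = 39.1, so about 39 visits. For 30 participants the ceiling is 30 × 39 = 1,170.
2. Calendar limit: the Results section has entry from June 2024 to July 2025 and collection ending in December 2025, which leaves about 18 down to 5 months. If entry was uniform (an assumption), the mean available time is (18 + 5)/2 = 11.5 months = 350 days, or 350/14 = 25 visits.
3. Stopping at the first exacerbation: the Abstract ends wear at that event. With a constant hazard λ per month (an assumption) and available time uniform on 5 to 18 months, mean follow-up = (1/λ) × [1 − (e^(−5λ) − e^(−18λ))/(13λ)]. The range of 0.5 to 3 events per person-year comes from Patient Population Size.
   - λ = 0.5/12 = 0.0417: (0.8119 − 0.4724)/0.5417 = 0.627; (1 − 0.627)/0.0417 ≈ 9.0 months, about 19 visits.
   - λ = 3/12 = 0.25: (0.2865 − 0.0111)/3.25 = 0.0847; (1 − 0.0847)/0.25 ≈ 3.7 months, about 8 visits.

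So 39 is a ceiling, and an average of 8 to 19 is more realistic under these assumptions. Withdrawals would lower it further. These counts show how regular the contact is; they say nothing about its effect on hours worn.

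**The case against.** The best defence is that *unsupervised* describes daily wear between visits and that *reminders* means automated prompts. No section describes the researcher telling anyone to wear the device, and alerts are off. The visits are also disclosed, in the Abstract among other places, and both the Methods overview and Strengths and Limitations admit that being observed may change behaviour.

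Part of this stands. That a visit works as a prompt is an inference, though a reasonable one when the visit includes questions on adherence. The request that "participants will be asked to sync data daily via Bluetooth" and the daily charging are weak evidence of supervision, because 24-hour storage and a 24-hour battery make them necessary; they bear on burden, not on oversight.

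The rest does not rescue the wording. The paragraph does not confine its claim to the days between visits, and those days all lie within the visit cycle. The caveats on observation give examples such as disease awareness, medication use, smoking and provider behaviour, and do not mention device wear. Nor does disclosing the visits elsewhere correct a specific description that conflicts with them.

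Stronger readings are tempting and should be resisted. A reader might infer that adherence is not measured at all; it is, since days and hours worn are recorded. A reader might reject the whole quoted phrase; the part on enforced schedules is sound. A reader might call the observed wear time an upper bound for unsupported use; that is plausible, but nothing in the article establishes it.

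**Conclusion.** The inconsistency is real and limited to the description of a secondary, descriptive outcome. Two of the three properties in the quoted phrase, the lack of supervision and the lack of external reminders, do not fit the visit schedule as written. The denial of burden or obligation conflicts with the article's own account of what volunteers must do. The wear-time data will be valid for use with fortnightly researcher support and cannot carry a conclusion about use without it.

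This rests on the visits taking place as described. The visit averages rest on uniform entry, a constant event rate and wear ending at the first event, but the conclusion does not depend on them. Event confirmation, the CUSUM analysis and the sample size are untouched. The correction is worth making before adherence is reported, because it changes to whom the result applies.

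**What to change.** In the last paragraph of Quantitative Analysis, replace *unsupervised* and *without external reminders* with wording such as *with fortnightly researcher visits and no enforced wearing schedule*. Reconcile the statement that no burden or obligation is imposed with the expectations in Potential Challenges and Alternatives. Limit the conclusion on real-world applicability to use with that support, and name the visits as a limitation.

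As an option, tabulate daily wear hours by days since the last visit, within participant, from the existing timestamps. This is a descriptive check for decay within a visit cycle. The report should say that a flat profile does not show that visits had no effect: a sustained rise from being visited at all would not appear, and expecting the next visit could lift wear late in the cycle.

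The cost is a change of wording and, if wanted, one table from data already collected. The adherence claim becomes slightly less favourable.

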### Ethical Considerations

This study complies with the Declaration of Helsinki [32] and adheres to Good Clinical Practice guidelines [33]. Participation in the study is completely voluntary, and participants may withdraw at any time without providing a reason, with no impact on their future medical care. Ethical approval for the study was granted by the NHS London - Stanmore Research Ethics Committee (Protocol number UEC23/71; IRAS project ID 32,823), and the study has been registered on ClinicalTrials.gov (NCT06419062). If there are any significant deviations from the study protocol, the investigator will submit an amendment for further approval by the ethics committee. No participants were compensated during their involvement in the study.

### Data Management

All data collected in this project will comply with the General Data Protection Regulation, the Caldicott Guardian principles, and the NHS Code of Confidentiality. Personal health data will be anonymized or pseudonymized wherever feasible and stored securely using encrypted electronic platforms. Short questionnaires completed by volunteers will be anonymized with unique numerical codes, and data will be transcribed into encrypted files. Researchers will adhere to the confidentiality policies of the University of Strathclyde and the UK General Pharmaceutical Council.

Anonymized physiological data will be securely stored within the Fourth Frontier Technologies Ltd cloud system, in full compliance with UK data protection and general data protection regulations. Data analyzed or generated at the University of Strathclyde will be securely stored within the university’s encrypted cloud infrastructure.

Each participant will be assigned a unique project identity code to ensure anonymity. The mapping file linking participant identity codes to personal information will be stored electronically in an encrypted cloud folder, with a physical backup kept in a locked filing cabinet at a secure university location. Access to these files will be strictly limited to the PhD researcher and their academic supervisor.

Hard-copy questionnaires completed by participants will be stored in a lockable briefcase until transferred to a secure university facility. Within 10 working days, responses will be transcribed into an encrypted digital file on the university cloud system, after which the physical copies will be shredded and disposed of through a university-approved confidential document disposal service.

To maintain confidentiality, all personal information will be pseudonymized, ensuring that no individual can be directly identified in the unlikely event of data loss. A unique email address and study ID will be generated for each participant to further protect identity. Within the Frontier dashboard, all uploaded physiological data are anonymized and accessible only via these identifiers.

For data processing and analysis, physiological recordings will be downloaded as CSV files from the Frontier dashboard for each activity session. All analyses will be performed independently of the manufacturer’s proprietary platform using open-source analytical tools such as Excel, Minitab, and Python. The Frontier device automatically uploads raw physiological data directly to the secure cloud without alteration. Although raw data are initially stored on the Frontier cloud, copies of all exported files will be securely downloaded and stored in the University of Strathclyde’s OneDrive system for independent analysis.

The University of Strathclyde will act as the data controller, and Fourth Frontier Technologies Ltd will act solely as the data processor, providing secure data transmission and temporary cloud storage during participant involvement.

## Results

Following ethical approval of the study protocol, the first patient was enrolled in June 2024, and recruitment was completed in July 2025. Data collection is ongoing and is expected to be completed by December 2025, within the planned 18-month study period. Statistical analysis is being conducted simultaneously with data collection. Final results are expected to be submitted for publication in January 2026. The findings, regardless of whether they are positive or negative, will be disseminated through peer-reviewed journals.

## Discussion

### Strengths and Limitations

There are no direct potential benefits to the patients while they participate since it is only an observational study. However, the research team will periodically review participants’ physiological data as part of the ongoing analysis. If the biometric data indicate a potentially concerning clinical pattern, the participant’s health care provider will be informed, which may prompt an unscheduled but potentially beneficial clinical intervention. There is also the possibility that agreeing to participate in the study may result in a “Hawthorne effect,” where there is a change in behavior as a response to observation and assessment either by the volunteer themselves (eg, better medication adherence, cessation of cigarette smoking) or by their health care provider (eg, more frequent monitoring or review of their medication).

The size of the cohorts and the duration of the study might not be enough to get accurate and expected results, but this is typical for most pilot studies, as we intend to determine the correct size and duration of the study required for expected results, which can be further used to plan future longitudinal studies. This can be partly mitigated by attempting to recruit people who are at high risk of exacerbation.

Previous studies have demonstrated that physiological changes, particularly increases in HR and RR, can occur up to 72 hours before an eCOPD event, supporting the feasibility of detecting early physiological alterations. However, these studies did not characterize these changes as continuous signal trends or apply them for the prediction of exacerbation onset. The present study aims to address this gap by identifying early physiological deviations that may serve as negative predictive signals and by exploring how these could inform the timely initiation of therapeutic interventions. Furthermore, by monitoring when physiological parameters return to baseline, this study has the potential to evaluate the effectiveness of treatment and the dynamics of recovery following an eCOPD event.

### Potential Challenges and Alternatives

The potential risks to participants are considered to be low or mild. Volunteers will have to continuously wear the device (Frontier X2). This may be associated with minor discomfort of the device being situated on their chest that may cause mild positional discomfort while undertaking certain activities, such as having to adopt an alternative sleeping position. The device is secured to the chest by an elastic chest strap, composed of a hypoallergenic material, although there is still a small possibility that it may cause a skin irritation if it is worn for prolonged periods in the same position.

The device has a battery life of 24 hours and can be fully recharged in 45 minutes. Users will be provided with the necessary equipment for charging the device and are expected to charge their device every 24 hours. This can be a burden for participants. Volunteers will be expected to complete a 10-minute symptom questionnaire every 2 weeks to see if this correlates with device biometric data capture. This questionnaire will be collected when the PhD researcher undertakes a site visit to the volunteer’s house to check the battery for the device and to provide any additional technical support. These would discontinue if there were any discomfort.

The non-invasive physiological measurements involve minimal burden.

### Conclusions

This study aims to build upon the limited existing validation of the Frontier X2 device for monitoring patients with COPD in real-life settings. The continuous monitoring capabilities of the device may support earlier clinical interventions, reducing the need for hospital admissions and improving patient outcomes. By shifting the focus from reactive to proactive care, such technologies have the potential to enhance clinical management and reduce morbidity and mortality rates associated with COPD.
